### Blood draws and candidate biomarkers

Left over blood samples of routinely collect blood tubes on admission will be immediatly centrifuged, aliquoted and frozen at -20C for later batch analysis of blood various biomarkers. The results of this analysis will not be available at the time of hospitalization of the patients and, thus, physicians and patients will be blinded to their results.

We will examine blood markers from different distinct biologic pathways as candidate biomarkers. Thus, we will assess markers of infection, inflammation, organ dysfunction, endothelial dysfunction, vasodilation / infection-control, stress hormones, cardiac dysfunction, nutrition, and kidney function, which all have been shown to predict adverse outcomes in different types of medical conditions (Table 
1). Depending on the expected benefit from a literature research, the available funding and logistic support, we will decide which markers should be analyzed in the stored aliquots.

**Table 1 T1:** Candidate parameters for improved diagnostic and prognostic patient assessment

**Candidate parameters**	**Pathophysiological concept / Previous research findings**	**Ref.**
**Infection marker** (PCT)	CALC I-gene associated hormokine of bacterial infections; correlates with infection severity and risk for bacteremia; responsive over time; established for antibiotic stewardship in respiratory tract infections and sepsis; moderate prognostic accuracy	[38-46]
**Inflammatory markers** (CRP, WBC)	Increase in response to inflammation and infection; low specificity and moderate sensitivity; low prognostic accuracy	[47-49]
**Organ dysfunction markers** (Lactate, coagulation, liver)	For progression of sepsis to severe sepsis with organ dysfunction; lactate is the recommended biomarker for early goal directed resuscitation therapy	[50-52]
**Endothelial activation markers** (VCAM-1, ICAM-1, E-selectin, PAI-1, sFLT-1, ET-1)	Marker panel correlates with vascular dysfunction, with sepsis severity and sepsis-related mortality; highest markers in septic shock; marker are dynamic over time and drop when patients condition is improving	[51,53-58]
**Vasodilation / infection markers** (Pro-adrenomedullin)	CALC V-Gene associated hormokine with high prognostic accuracy in pneumonia and sepsis in the ICU setting; significantly improves pneumonia risk scores (PSI, CURB65) based on OPTIMA II study	[17,18]
**Stress markers** (vasopressin precursor [copeptin], cortisol)	High prognostic accuracy in respiratory infections and sepsis; significantly improve previous pneumonia risk scores (PSI, CURB65)	[18,59,60]
**Cardiac dysfunction markers** (Natriuretic peptides: BNP, )	Correlate with cardiac dysfunction / cardiovascular stress; moderate to high prognostic accuracy	[61,62]
**Kidney dysfunction** (Urea, creatinine, NGAL)	High correlation with kidney dysfunction and increase in (pre) shock; also correlate with (septic) kidney injury	[63]
**Blood cells** (red cell distribution width)	Measure of variability of red cells; associated with in-hospital and ICU mortality	[64-66]
**Nutrition** (Albumin, pre- albumin, vitamin D)	Markers of nutrition have been shown to correlate with the general condition of patients and the risk of needing nursing care.	[67]

### Ancillary projects

Within this study, we have several ancillary projects focusing on different aspects of patient care in this medical population.

First, we will look at costs from different perspectives, i.e. patient, society perspective, insurance perspective and hospital perspective. We will collect detailed cost data as well as resource use data. Based on the daily clinical assessment we will have good estimates how length of stay (LOS) could be reduced in patients without increasing their risk, i.e. at the time patients are classified as “medically stable” by the treating physician team. We will develop cost models using DRG reimbursements to evaluate the potential in savings.

Second, within a subset of patients we will focus on psychological distress defined as negative psychological reaction which may pre-exist or develop in the context of an acute disease potentially involving a variety of affective, cognitive, and behavioral reactions, such as fear, sadness, anxiety, frustration, or non-compliance. In this ancillary project we aim to explore the prevalence and course of patients’ psychological distress on ED admission and within the hospital stay. To measure psychological distress we will use several validated instruments including the Distress Thermometer (DT)
[68,69] and the positive and negative affect schedule (PANAS)
[70]. Beside general distress our focus will particularly lie on anxiety and depression assessed with the Patient Health Questionnaire-4 (PHQ-4)
[71]. Additionally we will explore the relation of psychological distress with health outcomes (mortality, comorbidity, health-related quality of life, LOS among other) 30 days after admission. Finally, we aim to further delineate the role of specific patient’s psycho-social resources (personality, social support, age, sex, SES, medical diagnosis) with regard to distress and health outcomes.

### Statistical considerations and sample size

The purpose of this study is to develop an improved triage tool based on three distinct algorithms for (a) estimation of treatment priority (model 1), (b) prediction of medical risk (model 2) and (c) risk of post-acute care needs (model 3). For this purpose we have defined three distinct binary endpoints (i.e. high vs. low triage priority, adverse medical outcome within 30 days, post-acute care need) for which independent prediction rules will be developed using a similar approach for each one. However, based on the published literature, different candidate parameters will be considered as predictors for inclusion into the models.

In brief, for each algorithm we will select a parsimonious set of parameters from a comprehensive list of candidates including vital signs, clinical / socio-demographic predictors, blood markers, the MTS and the PACD. For blood markers we will focus on proADM and urea as the most established prognostic markers; however, we will also consider other markers for completion based on the availability of routine data (Table 
1). We will use multivariable logistic regression analysis and different selection techniques including stepwise regression, Lasso among others
[72]. We will also compare the non-parametric CART analysis to decide if a simpler algorithm would qualify. Improvements in the area under the receiver operating curve (AUC) and reclassification statistics will inform about the benefit of adding parameters to the model
[72,73]. We will apply split sample validation (training and validation set with a ratio of 1:1) and present goodness of fit statistics to assess robustness and internal validity. Based on these results, we will derive weighted admission risk scores for the three main models, which can be used for later decision making (Figure 
1). We will also look at subgroups to investigate differences in performance between main diagnoses and socio-demographic factors (age, gender) by inclusion of interaction terms into the logistic models.

For our model 1 (treatment priority), we will use adjudicated initial triage priority as the endpoint of interest (low vs. high triage priority) as defined above. As the MTS is well established for this purpose, we will first investigate the ability of the MTS to identify high priority subjects. We will then investigate whether addition of clinical parameters, vital signs and blood markers improve the MTS using statistical approaches outlined above. In a second step, we will investigate the performance of the MTS in subgroups of patients, i.e. stratified by initial admission diagnosis (e.g. myocardial infarction, congestive heart failure, infection, falls, lung embolism), by main clinical complain (e.g. dyspnea, fever, cough, pain) and by age quartiles, we will include interaction terms to study whether the association of the MTS and / or biomarkers varies across subgroups (effect modification). If significant effect modification is found, we will adapt the risk score to certain admission diagnoses.

For our model 2 (adverse outcome within 30 days) we will focus on death or ICU admission as the main outcome, in accordance with established risk scores (such as the pneumonia severity index or the CURB65 score)
[9]. In previous research
[18,27,34,35] we found that specific blood biomarkers (i.e. proADM) have very high prognostic accuracy in the range of clinical risk scores, and that this is true across different medical conditions. However, other “baseline” factors, such as age and comorbidities are likely providing prognostic information beyond that of blood markers. Thus, it is a promising approach to combine these factors in a combined risk model.

Our model 3 (post-acute care needs) will focus on care needs in patients after hospital discharge. The PACD score was developed for this purpose. However, the PACD focuses mainly on care needs of patients prior to hospital admission and availability of help in the home setting, but not as much on the current medical situation. It is therefore possible that addition of parameters reflecting the severity of disease (vital signs, blood markers) or the nutritional condition (blood markers) further improves its accuracy. We will therefore start with the PACD and investigate whether addition of other parameters significantly improves its accuracy as outlined above.

We aim to include a total of at least 5000 patients over the course of 12 months, with expected rates for high treatment priority of 20% (n=1000), for adverse outcomes of 10% (n=500) and for post-acute care needs of 20% (n=1000). This will provide 50–100 degrees of freedom for each model (with 10 cases in the data set per degree of freedom in the statistical model), and thus high power for the calculation of the main multivariate models overall, in pre-defined subgroups and after inclusion of interaction terms.

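### Testing effect modification by age in quartiles is less efficient than keeping age continuous; for a linear interaction, unordered quartiles cost about 15 to 23 points of power

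*Protocol article*

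**What the plan says.** All of this stands in the Protocol article under Statistical considerations and sample size.

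- **Model 1, second step.** MTS performance is examined in subgroups, first "stratified by initial admission diagnosis (e.g. myocardial infarction, congestive heart failure, infection, falls, lung embolism"), then by main complaint, then by age: "by age quartiles, we will include interaction terms to study whether the association of the MTS and / or biomarkers varies across subgroups". This is the only place where a form for age in an interaction is given. Whether the quartiles are unordered categories or an ordered score is not stated.
- **Consequence.** "If significant effect modification is found, we will adapt the risk score to certain admission diagnoses". No adaptation by age is described.
- **All three models.** Subgroup differences are also to be studied for "socio-demographic factors (age, gender) by inclusion of interaction terms into the logistic models", with no form for age.
- **Size.** The recruitment target is 5000 or more patients within a year. The article expects 1000 high-priority patients (20%), 500 adverse outcomes (10%) and 1000 patients with post-acute care needs (20%). From this it concludes: "This will provide 50–100 degrees of freedom for each model (with 10 cases in the data set per degree of freedom in the statistical model"). The same sentence adds that power is high, including once interaction terms are added. No interaction effect size, alpha or power figure is given.

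**The concern.** Age is a continuous measurement. Grouping it at sample quartiles before interacting it with the MTS or a marker has two costs. Variation in age within each quartile is ignored. And if the groups are unordered, a question that could be put with one parameter per marker is put with three. For an association that changes gradually with age, both costs lower the chance of seeing the change.

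What is at stake is the conclusion on effect modification by age. A non-significant result from a weak test may be read as evidence that the MTS and the markers work equally well in young and old patients. That sits poorly with the article's claim of high power for interaction terms.

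**Working it through.** **1. The article's own figures.** 5000 × 20% = 1000 events, and 1000 / 10 = 100 df. 5000 × 10% = 500 events, and 500 / 10 = 50 df. The stated 50 to 100 df reproduce. They give a ceiling on model size, not a power figure for any interaction, so there is no stated power to check.

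**2. Assumptions not in the article.** Two-sided alpha 0.05; age either normal or uniform, to give a range; a marker entered with one df; a reference power of 80% or 90% for the continuous test.

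**3. Information kept by quartiles.** This is the variance of the quartile means divided by the variance of age.
- Normal age: the standardised quartile means are ±0.325 and ±1.271, so the share kept is (0.325² + 1.271²) / 2 = 0.861.
- Uniform age: 1 − 1/4² = 0.9375.

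Grouping therefore discards about 6 to 14% of the age information.

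**4. Power for a linear interaction.** The noncentrality λ that gives 80% power on 1 df is (1.960 + 0.842)² = 7.85; for 90% it is 10.51. Multiply λ by the share kept, and refer it to a noncentral chi-square on 3 df (critical value 7.81, against 3.84 on 1 df).

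| Continuous, 1 df | Quartiles, 3 df, normal age | Quartiles, 3 df, uniform age | Trend across quartiles, 1 df |
|---|---|---|---|
| 80% | λ = 6.75: 57% | λ = 7.36: 61% | 74 to 77% |
| 90% | λ = 9.04: 71% | λ = 9.85: 75% | 85 to 88% |
| 99% | 93% | 95% | 98 to 99% |

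The loss with unordered quartiles is 19 to 23 points from 80%, 15 to 19 from 90%, and 4 to 6 from 99%. Most of it comes from the extra df: with no information lost at all, λ = 7.85 on 3 df gives 64.5%. A trend score loses about 3 to 6 points from 80% and 2 to 5 from 90%.

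**5. Simulation.** Logistic data with normal age and marker, event rate roughly 18 to 20%, 600 runs per setting, likelihood-ratio tests. At n = 5000, continuous against unordered quartiles: 74% against 50%, 90% against 69%, 99% against 93%. At n = 2500, the size of one half under the planned 1:1 split: 87% against 66%. With no interaction, both tests reject about equally often (4.5% at n = 5000, 6.5% at n = 2500). This agrees with step 4.

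**6. Other shapes.** Here 80% is the power of a 1-df test that knows the true shape. The spline is a 3-knot restricted cubic spline (2 df). Entries are normal / uniform age.

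| True shape of the interaction | Linear age | Spline | Unordered quartiles |
|---|---|---|---|
| Linear | 80 / 80% | 71 / 71% | 57 / 61% |
| U-shape | 5 / 5% | 68 / 70% | 26 / 48% |
| Flat to the median, then rising | 67 / 71% | 71 / 71% | 54 / 59% |
| Step at the top-quartile cut | 54 / 56% | 56 / 61% | 64 / 64% |
| Step at the median | 61 / 68% | 50 / 58% | 64 / 64% |

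The spline does better than unordered quartiles for every smooth shape here. Quartiles win only where the effect jumps exactly at a quartile cut.

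**The case against.** The strongest reply has four parts.

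*No consequence for the score is shown.* A reader might infer that the age test decides whether the risk score is adapted. The text does not support this. The adaptation sentence ends with admission diagnoses, and age is one of three stratifiers. For the same reason it cannot be said that sample-specific age cut points would be carried into the score: nothing puts them there. This part of the reply stands in full.

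*The size is conditional.* A reader might take a loss of about 20 points as a property of the plan. It needs a roughly linear interaction, unordered coding, alpha 0.05 and mid-range power, and the article fixes none of these. A trend coding loses little, and so does a very large effect. If the interaction is not linear, quartiles can beat linear age, as with the U-shape and both steps above. This stands too, and it is why the fix names a spline first. In the other direction, if the MTS entered as its five categories, the comparison would be 4 against 12 df and 80% would fall to 52 to 56%; the article does not state that coding either.

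*Continuous age is not excluded.* The general plan for age interactions names no form, and no sentence categorises age in the main models. So the point cannot extend to the main models. It does not remove the quartiles that are named for the model 1 interaction terms.

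*Nothing shows that power is inadequate.* Correct: with about 1000 expected high-priority patients and no stated interaction size, only relative efficiency can be shown. The calculation does not refute the claim of high power. It shows that the stated grouping works against it.

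**Conclusion.** The point holds in a limited form. The article names age quartiles for the model 1 effect-modification analysis, and a more efficient analysis of the same data is available. If the quartiles are unordered, a linear interaction detectable with 80 to 90% power on continuous age is detected with about 57 to 75%, a loss of 15 to 23 points. A 3-knot spline gives 71% where the linear test has 80%, so the gain from quartiles to spline is about 10 to 14 points in that case, and larger for a U-shape.

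These figures rest on the assumptions in step 2 of the working and on the unstated coding of the quartiles. The consequence is confined to a secondary subgroup conclusion about age; no effect on the derived score or on the main models is shown. It is a cheap improvement.

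**What to change.** In the model 1 interaction terms, enter age as continuous, with a 3-knot restricted cubic spline, or as linear if linearity is supported. Keep age quartiles only for descriptive tables of MTS performance.

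The cost is one line of analysis wording and no new data. There are two downsides. A spline interaction has to be read from a plot. And it has less power than quartiles if the effect jumps exactly at a quartile cut, which the article gives no reason to expect.

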## Discussion

### Potential limitations and bias

Treatment priority as adjudicated by the attending physicians at ED discharge is not a “hard” endpoint and may be subject to variation due to different levels of experience of physicians. Nevertheless, we have developed guidelines (Figure 
2) that will help to standardize adjudication based on previous research in this field
[37]. In addition, we will also look at other more objective endpoints (i.e. mortality, ICU admission, LOS). We will also collect information about physicians (years of experience, age, baseline “opinion” about risk scoring) and will thus be able to adjust the analysis accordingly. Also, physicians and nurses will not be blinded to the MTS, PACD and the risk assessment overall and thus may adapt their priority recommendation accordingly. This may overestimate the performance of the triage scoring systems. In terms of other blood markers and clinical parameters to improve the MTS, this bias will be minimal. Within this observational quality control project, we will not be able to demonstrate whether improved triage of patients translates into better management and improved outcomes; for this reason, we plan a second randomized controlled trial. While most prognostic blood markers (including proADM) are now commercially available within 1–3 hours, faster point-of-care tests are currently being developed that would enable measurement of marker within minutes, similar to a glucose measurement. This will further improve bedside use of these markers in the near future trial.

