### Endpoints

To improve management of patients at the earliest time point of ED admission, we aim to develop a triage algorithm based on three distinct decision rules for (a) assessment of triage priority, (b) need for hospitalization and (c) post-acute care needs as shown in Figure 
1. We therefore have three distinct main endpoints:

(a) Initial triage priority adjudicated by two independent ED physicians. Similar to a previous study
[37], the physicians will evaluate what the real degree of urgency (“Goldstandard”) would have been, based on the ED data, results of diagnostic tests, and the final diagnosis. Specifically, the main question for the adjudicators will be “*under difficult circumstances*, *what is the maximum possible time that this patient would have been able to wait before being seen*?” with options of “patient could not wait”, 10 minutes, 30 minutes, 90 minutes, or 3 hours. To further standardize the adjudication, we have developed examples as demonstrated in Figure 
2. We will collapse the initial 5 priority categories into 2 categories (i.e. low [more than 10 min, class 3, 4 or 5] vs. high priority [less than 10 min, class 1 or 2]). The 2 adjudicators will answer this question in regard to a medical prognostic focus and to a patient comfort focus (i.e. pain). In case of disagreement, a third independent physician will review the case until consensus is reached.

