### Procedures and management of patients throughout the trial

All patient procedures are part of routine clinical care. Upon ED admission, a triage nurse will assess triage priority according to the MTS. Vital signs will be recorded and left over blood samples will be stored for later batch analysis of blood markers. The risk for post-acute care needs will be assessed with the PACD score per usual care. Patients will be reassessed daily during the hospital course for medical stability and readiness for discharge with an electronic tool as defined above (Visitentool). To assess patient outcomes, data from electronic medical records and from a patient quality questionnaire complemented with follow-up interviews at day 30 will be used. Below the detailed different steps of patient management are shown.

Step 1. Upon ED admission, all patients will be assessed by a designated triage nurse. MTS triage priority will be assigned based on the MTS as recommended
[7]. This will be entered into the clinical information system along with information about main complain, vital signs and clinical variables. The triage nurse will also assess the PACD on admission.

Step 2. In all patients, the triage nurse will perform a standardized blood draw for routine measurement of blood chemistry per usual care; left over samples will be aliquoted at the center of laboratory medicine and used for later batch analysis of biomarkers.

Step 3. Upon ED discharge, the attending ED physician will adjudicate a medical triage priority based on all medical results available at this time to all patients (high vs. low triage priority).

Step 4. Throughout the hospital stay, patients will be managed by physicians, nurses and social care in accordance to hospital guidelines according to the underlying medical condition. This will be at the discretion of the treating physicians, nursing and social worker staff, independent of the research team. During hospitalization, nursing scores will be collected per usual care and entered into the electronic medical system along with information about the planed care provided to patients after hospital discharge.

Step 5. All patients will be contacted 30 days after hospital admission for a telephone interview with a predefined questionnaire to assess vital and functional status, hospital readmission, as well as quality of life, care needs at home and satisfaction with care provided.

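### The protocol calls reference-standard bias minimal for added blood markers and clinical parameters in model 1, but this can hold only for batch-assayed markers that clinicians do not see

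*Protocol article*

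**What the plan says.** All places are in the protocol article.

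- **Endpoints:** two independent ED physicians judge the real urgency of each case "based on the ED data, results of diagnostic tests, and the final diagnosis", with a third physician if they disagree. This is the outcome of model 1.
- **Procedures, Step 3:** "the attending ED physician will adjudicate a medical triage priority based on all medical results available at this time to all patients". The Abstract and the limitations section also name the attending ED physician.
- **Procedures, Steps 1 and 2:** the MTS category, main complaint, vital signs and clinical variables go into the clinical information system together. In all patients "the triage nurse will perform a standardized blood draw for routine measurement of blood chemistry per usual care".
- **Statistical considerations:** model 1 starts from the MTS and asks whether clinical parameters, vital signs and blood markers improve it, judged by change in AUC and by reclassification. "For blood markers we will focus on proADM and urea as the most established prognostic markers"; other markers depend on what routine data offer.
- **Blood draws and candidate biomarkers:** for the stored samples analysed later in batch, "physicians and patients will be blinded to their results".
- **Potential limitations and bias:** "physicians and nurses will not be blinded to the MTS, PACD and the risk assessment overall", and "This may overestimate the performance of the triage scoring systems". The next sentence is the one at issue: "In terms of other blood markers and clinical parameters to improve the MTS, this bias will be minimal".

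**The concern.** A predictor that helps to form the reference standard will tend to agree with it, whatever its real relation to urgency. This is incorporation bias. The limitations section recognises it for the triage scores, then dismisses it for two groups of added predictors. One of these, clinical parameters, is in the adjudicator's hands by the protocol's own account.

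There is also a consequence that the section does not draw. If the MTS looks better than it is, less is left for any added marker to explain. A marker that nobody saw can then look less useful than it is.

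Model 1 exists to decide what to add to the MTS. If visible and hidden candidates are measured on unequal terms, the choice between, say, vital signs and proADM may reflect who saw what. The derived algorithm is meant to go into a later randomised trial, so that choice would carry forward.

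**Working it through.** **1. Which candidates can inform the endpoint?**

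| Candidate addition to the MTS | Before the adjudicator? | Basis |
|---|---|---|
| Vital signs, clinical parameters | Yes | Part of the ED data (Endpoints); entered at triage (Step 1) |
| Routine chemistry, e.g. urea | Very likely, by inference | Measured routinely in all patients (Step 2); diagnostic results are used (Endpoints, Step 3). No passage says that the urea result is in the file |
| Markers assayed later from stored samples, e.g. proADM | No | Blinding stated (Blood draws) |
| MTS (the comparator) | Yes | Stated (Potential limitations and bias) |

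The limitations sentence covers the first three rows with one statement. Only the third row supports it, and only as regards inflation.

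**2. The protocol's own figures.** It gives none for this bias. Its planning figures reproduce: 5000 × 0.20 = 1000 high-priority patients and 5000 × 0.10 = 500 adverse outcomes.

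**3. Inflation of the comparator, which the protocol concedes.** Inputs from the documents are 1000 high- and 4000 low-priority patients, and 67% MTS sensitivity (Background, from small earlier studies). Assumed: 80% specificity, and adjudicators who follow the MTS in 20% of truly discordant cases.

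- Starting table: TP 670, FN 330, TN 0.80 × 4000 = 3200, FP 800.
- Moved by anchoring: 0.20 × 800 = 160 from FP to TP, and 0.20 × 330 = 66 from FN to TN.
- Apparent sensitivity = 830 / (830 + 264) = 75.9%. Apparent specificity = 3266 / (3266 + 640) = 83.6%.
- With 10% anchoring: 750 / 1047 = 71.6% and 3233 / 3953 = 81.8%.
- With specificity 70–90% and anchoring 10–20%, apparent sensitivity runs from 710 / 1007 = 70.5% to 910 / 1174 = 77.5%.

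This sizes the MTS baseline only. It says nothing about the increments.

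**4. Effect on the increments (illustrative simulation).** 200,000 patients, 20% high priority. Adjudicated urgency = true urgency + noise (SD 0.5) + wM × MTS + wV × visible predictor. A weight above zero means influence beyond what true urgency warrants. Assumed correlations with true urgency are 0.5 for the MTS and 0.4 for each added predictor. Gains are AUC differences over the MTS alone, from logistic models.

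| wM | wV | AUC, MTS alone | Gain, visible predictor | Gain, blinded marker |
|---|---|---|---|---|
| 0 | 0 | 0.725 | 0.037 | 0.038 |
| 0 | 0.15 | 0.725 | 0.070 | 0.038 |
| 0 | 0.5 | 0.718 | 0.143 | 0.037 |
| 0.15 | 0 | 0.773 | 0.028 | 0.028 |
| 0.5 | 0 | 0.854 | 0.016 | 0.016 |
| 0.15 | 0.15 | 0.771 | 0.054 | 0.029 |
| 0.5 | 0.5 | 0.832 | 0.078 | 0.018 |
| 0.3 | 0.15 | 0.809 | 0.043 | 0.023 |

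In every row where the MTS influences the rating, the blinded marker's gain is too small. The visible predictor's gain can be too large (up to 0.143), nearly right (0.043 against 0.037) or too small (0.016), depending on the two weights. Correlation sets 0.5/0.3 and 0.6/0.4 gave the same signs.

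**The case against.** **The sentence may be narrower than it looks.** Read with the two sentences before it, the bias in question is adaptation to the MTS and PACD, and the claim is that such anchoring hardly inflates the added parameters. For batch-assayed markers that is fair, and anchoring on the MTS makes their increment conservative. This stands. It does not rescue clinical parameters, which the sentence names and which the adjudicator reads directly. Nor does it tell the reader that the increments are affected at all.

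**Part is already disclosed.** The protocol states that staff are not blinded to the MTS, says that the scores may be overestimated, and promises a look at mortality, ICU admission and length of stay. This stands too, so the MTS inflation in itself is not the finding. What is missing is its effect on the increments, and any link between those objective endpoints and a check of the model 1 increments.

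**A full-information expert standard is deliberate.** Judging real urgency from everything known is a recognised choice, adapted here from a previous study. Visibility does not by itself prove bias, since vital signs may properly inform true urgency. This is why the point is openness to bias and not a demonstrated distortion.

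**Stronger readings that a reader might infer.** One is that visible predictors are certainly overstated. The documents do not support that, because the two influences partly offset and their weights are unknown. Another is that adjudicators demonstrably see urea; this is a plausible inference and no more. A third is that hiding the MTS would cure the problem. It would not: vital signs and test results stay in view, and an attending physician working in the system that holds the MTS cannot be masked through a file.

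**Conclusion.** The sentence is wrong as written for clinical parameters and vital signs and, by inference, for routine chemistry. The protocol's own description of the endpoint puts these in front of the adjudicator. It is defensible for batch-assayed markers as regards inflation, but their increment over the MTS may be understated.

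The size cannot be derived from the documents, nor can the net direction for visible predictors. The simulated AUC gains rest entirely on assumed correlations and weights. They show what can happen, not what will. The apparent-sensitivity figures rest on assumed specificity and anchoring, and treat the 67% from earlier studies as true in this cohort.

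Only model 1 is affected. The endpoints of models 2 and 3 are not adjudicated in this way, and the sample size does not change. The point should be corrected because it bears on which predictors enter the algorithm and on what may be claimed for them.

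**What to change.** 1. **Rewrite the limitation**, for example: *Inflation from the reference standard is expected to be minimal only for batch-assayed markers unavailable to clinicians. Increments for vital signs, clinical parameters and routine laboratory values may be biased, and those of hidden markers may be understated because adjudicators can see the MTS.*
2. **Add one table** with the increment of each predictor group over the MTS, against both adjudicated priority and death or ICU admission, which is already collected. The check is partial: 30-day risk is not the same as urgency, and ICU admission is itself a clinical decision.
3. **Make no head-to-head claim** between visible and hidden markers on the adjudicated endpoint alone.
4. **Reconcile who adjudicates.** The Endpoints section has two independent physicians; the Abstract, Step 3 and the limitations section have the attending ED physician. Where independent adjudicators read a file, leave the MTS category, the MTS flowchart and the PACD out of it. This helps with anchoring on the scores only.

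Cost: a rewritten limitation, one extra table and slightly more file preparation. No new patients or data are needed. Recruitment had already started, so item 4 can apply only to files not yet adjudicated; items 1 to 3 apply whoever adjudicates.
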